### Arm B

Patients in ARM B will be treated with SRT on prostate alone at a total dose of 36.25 Gy administered daily or every other day in 5 fractions (7.25 Gy/fraction). SRT treatment planning procedure and ADT prescription are diffusely explained in study protocol.

### Source of the study drug

Triptorelin 22.5 mg and Bicalutamide 50 mg will be provided by the sponsor institution and delivered by express courier to the pharmacy of each Institution.

Bicalutamide will be directly delivered by the medical staff after adequate and comprehensive instructions (50 mg daily, starting from 7 days before LH–RH analog to 10 days after). Triptorelin will be administered directly by nurses or physicians as a single intramuscular injection at least the day before SRT starting, with an encorauged time of administration 90 days before SBRT for cytoreductive purposes (not mandatory).

### Outcome measures and study timeline

Concerning the timing of the study, the accrual time will be 3 years and the follow-up (FU) length will be 5 years.

Patients will be screened before treatment beginning concerning performance status (PS), Testosterone, digital rectal examination (DRE), PRO (IPSS, IIEF), QoL (EPIC 26 and EORTC PR 25). Screening will exploit an online dedicated platform (www.trialspa.it). After meeting every eligibility criteria, a centralized randomization procedure will be automatically performed with a dedicated in-house software.

RT will be started within 16 weeks from randomization.

ADT will be administered form 12 weeks before RT to immediately before RT.

Evaluation will be daily performed during SRT and the last day of treatment to assess acute toxicity (CTCAE 5.0). During the last day of treatment also PRO and QoL will be scored.

Subsequently, patients will be assessed at 1 months after SRT for PS, DRE, acute toxicity, PRO and QoL.

Afterwards, 3 months after SRT completion, PSA, PS and DRE will be assessed together with toxicity PRO and QoL. For the first year of follow-up, patients will be evaluated every 3 months.

After 12 months from the end of treatment, the FU will be every 4 months. Instead, it will be scheduled every 6 months starting 24 months after the end of treatment (Figure 2).

**Figure 2. F2:**
[figure not shown]
Pre-randomization and follow-up assessment of PSA, testosterone, toxicity, PRO e QoL questionnaires in details. PRO, patient reported outcome; PSA, prostate-specific antigen; QoL, quality of life.

### Patient and public involvement

Patients or the public were not involved in the design, or conduct, or reporting, or dissemination plans of our research.

## Statistical considerations

### Sample size determination

In the context of normofractionated, dose-escalated PC treatment, 5 years bDFS obtained with ADT and without ADT are reported to be 84 and 69%. Due to the lack of standardized use of ADT in SRT patients, we can estimate from preliminary data on intermediate- and high risk patients a difference in bDFS of 10% at 5 years. In ARM A (SRT +ADT), we expect a bDFS of 95% at 5 years, whereas in ARM B (SRT alone), we expect a bDFS of 85% at 5 years. Considering an α error of 0,05 (2-tailed) and a 1-β of 80%, a study sample of 310 patients, 155 patients for each arm will be necessary to detect a difference of at least 10% in the two groups with a power of 83.9%.

Freedom from biochemical/clinical progression will be compared by proportions, respectively of 85 and 95% of bDFS expected in two arms, according to the sample size hypothesized above. Estimates of event rates will be calculated using the Kaplan–Meier method. The Cox proportional hazard model will be used to adjust for risk group and important known prognostic factors. Gathered data will be analyzed using SPSS^®^ v. 26.0 software (IBM^®^).

### Acute and late toxicity

Acute and late toxicity will be summarized by the proportions experiencing grade ≥2 side-effects with comparisons made (where appropriate) using χ^2^ based tests or Fisher’s exact test if expected cell frequencies will be less than 5.

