**Results::**

Sample size is estimated of 310 pts. For acute toxicity and quality of life results are awaited after 6 months since last patient in, whereas, for efficacy end points and late toxicity mature results will be available 3–5 years after last patient in.

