Remarkably, in 2016, the randomized Phase III study from Bolla and colleagues demonstrated that combining short-course ADT with normofractionated EBRT improves 5 year bDFS and DFS over RT alone for intermediate and high risk PC patients (hazard ratio 0.52 and 0.63, respectively). Interestingly, there was a statistically significant reduction in 5 year local relapses rate from 6 to 2%, and in the distant metastasis rate from 7.6 to 4.4% (hazard ratio 0.37 in both cases) in the combination arm.^
10
^

Another reason which may explain the frequent omission of short-term ADT in unfavorable intermediate risk patients eligible for SRT could be related to concerns about the ADT side-effects. Also, in the context of SRT prospective studies identified an increased risk of acute and late GU toxicity in SRT + ADT arm, with a mechanism not completely clear.^
11
^ Interestingly, Bolla and colleagues in the former randomized, Phase III trial also performed a QoL analysis with HRQOL questionnaires (EORTC QoL questionnaires C30 supplemented with a QLQ-PR25) and showed no clinically relevant differences in HRQOL scores between the groups. As experienced ADT-related symptoms, as well, were more clinically evident and significantly worse in the ADT arm, at month 6 and at year 1, as sexual activity and functioning scales. However, no marked difference was seen between the arms from year 2 onward. Nevertheless, this trial did not consider the impact of ADT on endocrine homeostasis, as reported in a wide body of literature.^
12–14
^

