### Endpoints of the study

#### Primary end point

Primary end point will be to determine if there is any improvement in bDFS, defined as prostate-specific antigen (PSA) rising ≥2 ng ml^−1^ over PSA Nadir, following the Phoenix criteria for biochemical recurrence of PC (after primary RT) in patients treated with prostate SRT plus ADT (ARM A) compared to patients treated with SRT alone (ARM B).

Study end points are summarized in Table 1.

**Table 1. T1:** Study end points

PRIMARY END POINTS	SECONDARY END POINTS
Determine if there is any improvement in bDFS in patients treated with prostate SRT plus ADT (ARM A) compared to patients treated with SRT alone (ARM B)	DFS FFLR FFRR FFDM OS

bDFS, biochemical disease-free survival; FFDM, freedom from distant metastasis; FFLR, freedom from local recurrence; FFRR, freedom from regional recurrence; OS, overall survival.

All biochemical failures need to be confirmed with a second PSA detection meeting the criteria for failure. In addition, it is now recognized that a benign PSA bounce may be seen in up to 20% of patients after SRT, usually within the first 2 years.^
15
^

In some cases, the magnitude of the PSA bounce may be considered as high enough for the patient to be incorrectly classified as a PSA failure. To prevent this, for patients receiving SRT, PSA failure before 24 months after the treatment will require three consecutive PSA rises to resulting a clinical diagnosis of failure, or the start of further treatment (androgen deprivation therapy). Over 24 months, the definition of PSA failure for SRT will refer to the Phoenix definition described above (*i.e.* PSA nadir+2 ng ml^−1^).

QoL and patient reported outcomes (PROs) will be an exploratory end point and will be scored with questionnaires EPIC-26, EORTC PR 25, IPSS, IIEF in SRT + ADT and SRT alone arms.

Moreover, Clinician reported Acute Toxicity, assessed with CTCAE v. 5.0 scales and Clinician reported Late Toxicity, assessed with CTCAE v. 5.0 scales will be safety end points.

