## Discussion

In the context of localized PC, the evidence of a safe, effective and more convenient treatment will move the clinical and patient’s choice toward SRT. Advances in image guidance such as MRI-guided RT is a promising approach to increase the therapeutic index in this context.^
16
^ Remarkably, several recent studies, including clinical trials, have tested SRT efficacy on localized PC omitting ADT.^
5–7,15,17
^

Of note, ADT is widely recognized to improve outcomes in combination with standard and moderate fractionated RT for a subclass of intermediate- and high risk PC patients. Biological rationale of combining RT and ADT were reported in literature,^
10
^ although the role of ADT in the context of high dose-per-fraction schedule is still uncertain.^
18
^ Therefore, ADT effect in combination with normofractionated and hypofractionated RT is not clearly movable to ultra-hypofractionation.^
8,9
^

Recently, in high risk patients, the SHARP consortium prospectively evaluated 344 treated patients, with the aim to explore the efficacy and toxicity of SRT in the context of high risk PC. 72% of patients received ADT (investigator’s choice), with a median duration of 9 months. At univariate analysis, 4 years bRFS resulted significantly greater among patients treated with concurrent ADT but 4 years DMFS was not significantly different.^
11
^ Given the non-randomized nature of the studies included, selection bias may have influenced the choice to administer ADT. As a consequence, such variable did not enter in multivariable model. Differently, Jackson et al in a meta-analysis of over 6000 pts treated on prospective studies did not found any advantage for ADT use on bDFS, Remarkably, in both studies, ADT use was administered at investigator’s choice and therefore caution must be exercised in the interpretation of these results.

Regarding toxicity, multivariable logistic regression for acute and late toxicity showed that ADT use and 8 Gy per-fraction schedule were associated with higher risk of GU Grade ≥ 3. The physiopathogenesis of increased toxicity with ADT use is unclear. One of the hypothesis concerning both GU and gastrointestinal (GI) side-effects consists in the possible downstaging and shrinking effect determined by ADT that could contribute to an higher than expected dose to critical organs such as bladder and rectum.^
11,19
^

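### Late toxicity is to be compared as a crude grade ≥2 proportion at no stated time, although follow-up is staggered, so the reported rate will depend on the data cut and on attrition

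*Protocol article*

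**What the plan says.** The toxicity analysis is set out in a single sentence of the Protocol article, under the heading Acute and late toxicity: "Acute and late toxicity will be summarized by the proportions experiencing grade ≥2 side-effects". Comparisons, where appropriate, use χ² "based tests or Fisher’s exact test if expected cell frequencies will be less than 5". The same measure, threshold and tests apply to acute and to late events.

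Under Endpoints of the study, toxicity is a safety end point: "Clinician reported Late Toxicity, assessed with CTCAE v. 5.0 scales will be safety end points".

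Two other places fix the timing. Outcome measures and study timeline says that "the accrual time will be 3 years and the follow-up (FU) length will be 5 years". The Results paragraph of the abstract says that "for efficacy end points and late toxicity mature results will be available 3–5 years after last patient in".

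The Kaplan–Meier method is named under Sample size determination, in the paragraph on biochemical and clinical progression. It is not linked to toxicity. The Analysis plan gives 12 weeks, 6 months and 12 months as the times for quality of life and patient-reported outcomes. No such time is given for late toxicity.

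**The concern.** Late toxicity accumulates over years, so a proportion has a clear meaning only when every patient has been observed for the same length of time or when the method allows for unequal observation. A crude proportion does neither. With 3 years of staggered entry and a read-out that may come 3 years after the last patient in, the last men to enter will have been observed for 3 years and the first for the full 5. A man who dies or is lost at year 1 and stays in the denominator contributes a non-event for time in which he was not observed.

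The late rate is one of the figures a reader would set against any gain in biochemical disease-free survival. If its value moves with the date of the data cut and with the amount of attrition, it cannot be read as a risk at 2, 3 or 5 years.

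**Working it through.** **Inputs from the Protocol article.** Accrual 3 years, follow-up 5 years (Outcome measures and study timeline); late read-out 3 to 5 years after last patient in (abstract, Results); crude proportion with χ²/Fisher (Acute and late toxicity).

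**Assumptions.** The article gives no toxicity rate, so there is no figure of its own to reproduce. I assume uniform accrual, a constant hazard of a first late grade ≥2 event, and a 5-year risk of 20% in the absence of death and loss. I take the 5-year follow-up as a cap per patient.

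**Step 1. Hazard.** h = −ln(1 − 0.20)/5 = 0.0446 per year. The 3-year risk is 1 − 0.8^(3/5) = 12.5%.

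**Step 2. Range of follow-up at a 3-year cut.** Time since entry is uniform on 3 to 6 years. With the cap, two-thirds of patients have between 3 and 5 years and one-third have exactly 5.

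**Step 3. Crude rate at a 3-year cut, no attrition.**
- Mean event-free probability over 3 to 5 years: (e^(−3h) − e^(−5h))/(2h) = (0.8747 − 0.8000)/0.0893 = 0.837.
- Overall: (2/3)(0.837) + (1/3)(0.800) = 0.8245.
- Crude proportion: 1 − 0.8245 = **17.5%**. This lies between the 3-year risk (12.5%) and the 5-year risk (20%) and equals neither.

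**Step 4. The same cut with death plus loss at 4% per year (assumed).** Those who die or are lost stay in the denominator.
- k = h + 0.04 = 0.0846; the observed event probability by time t is (h/k)(1 − e^(−kt)), with h/k = 0.527.
- Mean of e^(−kt) over 3 to 5 years: (0.7758 − 0.6550)/(2 × 0.0846) = 0.714.
- Overall: (2/3)(0.714) + (1/3)(0.655) = 0.694.
- Crude proportion: 0.527 × (1 − 0.694) = **16.1%**.

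Part of this fall may be real. A death before toxicity does prevent the event. If all 4% were deaths, the 5-year cumulative incidence would itself be 0.527 × (1 − 0.655) = 18.2%; if all were losses, the target would stay at 20%. The crude rate at this cut is below either.

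**Step 5. A cut 5 years after last patient in, capped at 5 years.** Without attrition every patient has 5 years, and the crude rate is **20.0%**. With 2%, 5% or 10% attrition per year, (h/k)(1 − e^(−5k)) gives 19.1%, 17.8% and 15.9%.

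**Step 6. Comparison of arms.** Entry dates are balanced by 1:1 randomisation, so Steps 3 and 5 apply equally to both arms and create no difference by themselves. If, for illustration, loss were 2% per year in one arm and 5% in the other at equal true risk, the crude rates at the full 5-year cut would be 19.1% and 17.8%. That is a spurious difference of 1.3 points.

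**The case against.** The strongest reply is that the article gives a follow-up length of 5 years. If every man is followed for 5 years and the late analysis waits until 5 years after the last entry, the crude proportion is the 5-year cumulative risk apart from death and loss. That is right, and Step 5 shows it. But the abstract allows the read-out from 3 years, and the toxicity section does not tie the late analysis to completed follow-up. Even at 5 years, attrition still lowers the rate.

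A second reply is that the denominator is not defined, so counting early losses as event-free is itself a reading. This also stands, and the attrition figures are conditional on it. Dropping such men instead would not solve the problem, since it would discard their observed time.

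Third, toxicity is a safety end point and randomisation protects the comparison from staggered entry. That holds too: neither the sample size nor the primary analysis is touched, and no arm difference in death or loss can be shown from the article.

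A reader might go further and infer that all types of grade ≥2 event are pooled, so that the side-effects of androgen deprivation would produce an apparent excess in Arm A even with equal genitourinary and gastrointestinal toxicity. The document does not support this. It never says that types are pooled. The plural wording fits separate rates by organ class equally well, and such a breakdown is what an article leaves to the full protocol. An excess caused by androgen deprivation would in any case be a real effect of Arm A, and any size put on it would rest on assumed rates alone.

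**Conclusion.** The point holds for late toxicity only, as an inexpensive improvement of limited weight. The article does not merely leave the method open: it fixes a crude proportion and a test that ignores time, in a design with staggered entry and a read-out window of 2 years.

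For an assumed 5-year risk of 20%, the reported late rate would be 17.5% at a 3-year cut, about 16% with 4% per year death plus loss, and 20% only when all men complete 5 years. These figures rest on a constant hazard, uniform accrual, a 5-year cap, and retention of early losses in the denominator. A higher crude figure would require counting events beyond the stated 5 years, which I do not assume.

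The harm is mainly to the absolute late rate. A reader might infer that the comparison between arms is also biased. That would follow only if death or loss differed by arm, and nothing in the article establishes that it will.

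**What to change.** In the Acute and late toxicity section, separate the two analyses.

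- **Late toxicity:** report the cumulative incidence of the first grade ≥2 event, with death as a competing event and patients lost or still in follow-up censored. Give estimates with confidence intervals by arm at fixed times, for example 2 and 5 years. Compare arms by Gray's test or a cause-specific hazard ratio.
- **Acute toxicity:** keep the χ² or Fisher's exact test, since that window is short and nearly complete for everyone.

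Stating that genitourinary and gastrointestinal events are reported separately would be a useful clarification, but no more than that.

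The cost is a few sentences and a little more analysis of CTCAE data already being collected, provided that event dates are recorded. Competing-risk estimates may need software beyond the named package. No extra patients or visits are needed, and the sample size and primary analysis do not change.

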### Randomization

The study will employ a 1:1 randomization between Arm 1: Arm 2, and will be accounted for minimization with a balancing algorithm for two variables:age <70 ≥70,unfavorable intermediate- and high risk group.

Patients will be randomized in permuted blocks, with the size of the blocks known only to the statistician. The randomization sequence is known only to the statistician and uploaded into a restricted-access database (www.trialspa.it) housed on secure hospital servers at University of Brescia and Spedali Civili Hospital. The Local PI, before enrolling a patient, will access with a personal login ID and password the internet site to perform the screening procedure. If successfully completed, an automatic allocation for the patient ARM will be provided.

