## Methods and materials

### Trial design and allocation ratio

This is a multicenter, open label, randomized-controlled, Phase III study. Randomization will be 1:1 and will be accounted for minimization with a balancing algorithm for two variables:patients age <70 vs ≥70unfavorable intermediate risk and a subgroup of PC high risk group

In arm A, patients will be treated with prostate SRT to a total dose of 36.25 Gy in 5 fractions (consecutive or alternate days) plus 6 months of ADT consisting in LHRH analog (Triptorelin 22.5 mg). In arm B, patients will be treated with prostate SRT alone to a total dose of 36.25 Gy in 5 fractions (consecutive or alternate days) (Figure 1).

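### The article describes allocation both as minimisation and as a pre-made permuted-block sequence; one must be stated, and the analysis should then carry both balancing factors

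*Protocol article*

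**What the plan says.** Two sections of the article describe allocation.

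- Trial design and allocation ratio: "Randomization will be 1:1 and will be accounted for minimization with a balancing algorithm for two variables". The variables are age, split at 70, and risk group.
- Randomization, first paragraph: the allocation "will be accounted for minimization with a balancing algorithm for two variables", with the same two variables, the second being "unfavorable intermediate- and high risk group".
- Randomization, second paragraph: "Patients will be randomized in permuted blocks, with the size of the blocks known only to the statistician". It continues: "The randomization sequence is known only to the statistician and uploaded into a restricted-access database".

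The analysis is described under Sample size determination. There, "Freedom from biochemical/clinical progression will be compared by proportions", with no stratification or adjustment mentioned. The same paragraph adds: "The Cox proportional hazard model will be used to adjust for risk group and important known prognostic factors". The article does not say which of these two analyses carries the primary inference.

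**The concern.** Minimisation and permuted blocks differ in how each patient's arm is determined. Minimisation looks at the age and risk-group totals already in each arm and favours the arm that reduces the imbalance. It has no block size. A permuted-block list is drawn up before the first patient arrives and takes no account of those totals. Unless it is stratified, it balances overall numbers but balances age and risk group only by chance.

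A reader therefore cannot tell which procedure the trial uses, or whether the promised balance on the two factors is delivered. This matters for three reasons. The trial is open label and allocation runs on locally built software, so the written specification is what that software can be checked against. Predictability depends on different features of the two methods: the random element for minimisation, for which none is stated, and the block size for blocks. The matching analysis also depends on which method was used: if the trial forces balance on prognostic factors, the analysis should take them into account, and as written it does so only in part.

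**Working it through.** **Step 1. The two descriptions side by side.**

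| Feature | Minimisation (both sections) | Permuted blocks (Randomization, second paragraph) |
|---|---|---|
| What fixes the next arm | Current totals by age and risk group | Next entry on a prepared list |
| Block size | None | Exists, kept from sites |
| Arm sequence to upload | None | Exists, uploaded |
| Balance on age and risk group | By construction | Only if stratified; no stratification stated |

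Each column is a positive statement in the article, and they cannot both describe how a given patient is assigned. No sentence joins them.

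**Step 2. Reproduce the plan's power.** Inputs from Sample size determination: 5-year bDFS 85% and 95%, two-sided α 0.05, 155 per arm. For an unadjusted two-proportion test with pooled variance under the null:

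- null SE = √(2 × 0.90 × 0.10 / 155) = 0.03408
- alternative SE = √((0.85 × 0.15 + 0.95 × 0.05) / 155) = 0.03360
- power = Φ((0.10 − 1.96 × 0.03408) / 0.03360) = Φ(0.988) = 83.85%

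This matches the stated 83.9%. The design calculation is therefore that of an unadjusted comparison, and the allocation method does not enter it.

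**Step 3. Effect of leaving the balancing factors out of the test.** The article gives no risks by age or risk group, so these are assumptions: four equal age-by-risk strata with a mean control event rate of 15%. The treatment effect is a common odds ratio of (0.05/0.95)/(0.15/0.85) = 0.298. There were 20,000 simulated trials of 310 patients per scenario, with arms balanced within strata. An unadjusted two-proportion test is compared with a stratified (Cochran–Mantel–Haenszel) test.

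| Assumed control event rates | Type I error, unadjusted | Type I error, stratified | Power, unadjusted | Power, stratified |
|---|---|---|---|---|
| 15% in all strata | 4.8% | 4.7% | 85.3% | 85.3% |
| 8, 12, 18, 22% | 4.9% | 5.1% | 84.8% | 85.2% |
| 4, 8, 20, 28% | 4.3% | 4.9% | 83.1% | 84.3% |

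The Monte Carlo standard error at 5% is √(0.05 × 0.95 / 20,000) = 0.15 points.

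**Step 4. Check the direction by formula.** With perfect balance, the unadjusted test uses the total variance p̄(1 − p̄), while the difference varies only with the within-stratum variance. In the widest scenario:

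- total variance = 0.15 × 0.85 = 0.1275
- within-stratum variance = (0.0384 + 0.0736 + 0.1600 + 0.2016)/4 = 0.1184
- effective critical value = 1.96 / √(0.1184/0.1275) = 2.034
- type I error = 2 × (1 − Φ(2.034)) = 4.2%, in line with the simulated 4.3%

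**Step 5. A second simulation.** Minimisation with assignment probability 0.8 was simulated in 6,000 trials per scenario, for two assumed pairs of stratum failure risks. At 10% and 20%, type I error was 0.044 unadjusted and 0.048 stratified. At 5% and 25%, it was 0.039 and 0.047. Power at 5% and 25% with a hazard ratio of 0.316 was 0.852 and 0.863. The standard error at 5% is about 0.28 points, so the 0.044 to 0.048 contrast is weak evidence on its own. The direction agrees with Steps 3 and 4.

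**The case against.** The strongest objection is that this is a condensed article which refers to a full study protocol for detail, and that covariates and stratification of the test are normally settled there or in the analysis plan. For the covariate list this stands. It does not excuse the allocation text, which makes two incompatible statements rather than leaving something out.

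It can also be said that a prepared random list is compatible with minimisation if it serves to break ties or supply the random element. That is true in general, but the article says that patients are randomised in blocks and describes no such use.

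Three stronger readings are tempting, and the document does not support them.

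- A reader might infer that the primary comparison ignores both balancing factors altogether. The Cox model names risk group, age could fall under its other prognostic factors, and the article does not say that the proportions test is the primary inference.
- A reader might infer that concealment has failed. Randomisation is central and automatic after completed screening, with restricted access and a block size and sequence known only to the statistician. The conflict leaves the method unclear but shows no breach.
- A reader might infer that the open covariate wording overloads the Cox model. The Analysis plan calls the analysis event driven but gives no target number, and the full list may be fixed elsewhere, so this cannot be judged here.

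**Conclusion.** The contradiction is certain on the text: the article specifies two allocation methods and does not reconcile them.

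The analysis point is secondary. The proportions comparison states no adjustment, and the Cox model names one balancing factor and not the other. If the trial does balance on both, leaving them out makes the test at most slightly conservative, with type I error of about 0.04 to 0.05, and costs up to about 1 point of power. Those figures rest on assumed stratum risks and on balance being achieved. With no prognostic effect the difference disappears. If the software in fact runs unstratified blocks, balance on the two factors is not forced and this source of conservatism does not arise, which is a further reason to settle the method first. The sample size of 310 and the power of 83.9% stand either way.

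**What to change.** 1. Confirm what the allocation software actually runs before editing, so that the text is corrected to the practice.
2. State that one method in both Trial design and allocation ratio and Randomization, and delete the other description. Two options resolve the conflict equally well: minimisation on age and risk group with its random element stated (an assignment probability of 0.8 is one example), or permuted blocks stratified by age and risk group, which makes four strata. If a prepared list only feeds the random element of minimisation, say so.
3. Stratify the primary comparison by age (<70 or ≥70) and risk group: Cochran–Mantel–Haenszel if it compares proportions, stratified log-rank if it is time-to-event. Include both factors in the Cox model and move other prognostic factors to a sensitivity model.

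The cost is wording and one check of the software. No change to the sample size is needed.
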